**Design**

This study will be a cluster randomized controlled trial. Randomization at the patient level was considered, but deemed inapplicable due to the fact that one GP would have patients in both the control and intervention groups, thus leading to possible contamination bias. Randomization at the GP level was not possible, because most GPs work in group-practices and share patients, which would lead to a GP in the control group reading the reports of another GP that received the intervention. This would also lead to contamination bias. It was therefore decided to randomize on the GP cluster level, where GPs treating the same patients will be regarded as a randomization unit (usually 2 or 3 GPs).

GPs will be allocated into three groups:
1. Will receive no messages (control group)
2. Will receive messages that can be ignored without justification (intervention 1)
3. Will receive messages that can only be ignored with justification (intervention 2)

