**Sample size and analysis**

A power analysis showed that 300 patients are needed for a power of 0.8 when assuming a base adherence of 50%, an absolute effect size of 10% for intervention group 2 and 20% for intervention group 3, with a test significance level of 0.05. Because GPs are clustered for randomization, a correction for these clustering effects was introduced. For the cluster correction analysis, an intra-class correlation of .1 was assumed, based on studies using similar clustering ([15](#_ENREF_15)). This resulted in a required sample size of approximately 500 patients to result in an effective sample size of 300.

When data collection has been concluded, differences in adherence percentages will be calculated per GP cluster. A chi-square test will be used to compare the differences in the three groups.

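### The only stated primary test is an ordinary chi-square with no cluster adjustment; on patient counts its true error rate would be about 17% at the plan's own design effect, not 5%

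*Protocol*

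**What the plan says.** The Design section sets the unit of randomisation: "It was therefore decided to randomize on the GP cluster level". There are three arms: no messages, messages that may be ignored freely, and messages that may be ignored only with a stated reason.

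Under Sample size and analysis, the protocol gives an unclustered requirement ("A power analysis showed that 300 patients are needed for a power of 0.8"), "with a test significance level of 0.05", and assumes "an absolute effect size of 10% for intervention group 2 and 20% for intervention group 3" over a base of 50%. It then corrects for clustering: "an intra-class correlation of .1 was assumed", which takes 300 patients to about 500.

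The analysis follows in two sentences. First, "differences in adherence percentages will be calculated per GP cluster". Then, "A chi-square test will be used to compare the differences in the three groups". No design-effect adjustment, cluster-level test, mixed model or generalised estimating equation is mentioned. The Outcomes section defines the primary outcome as a proportion of patients, compared between the three groups.

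The only cluster count is in the Population section: 18 clusters with 35 GPs, described as the initial set. No average cluster size is given.

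**The concern.** The protocol treats patients in the same cluster as correlated when it sets the sample size, then names a test that assumes independence. The sentence about per-cluster differences does not repair this. There are two natural ways to carry out what is written:

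- A chi-square test on adherent and non-adherent patients by arm. This fits the primary outcome as defined, but it counts correlated patients as independent.
- A chi-square test on cluster percentages, or on differences between them. These are not counts, so the chi-square reference distribution does not apply.

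Neither gives a valid primary p-value. At stake is a false claim that guideline adherence differs between the arms, made more often than the stated 5% level allows.

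**Working it through.** **Inputs.** From Sample size and analysis: significance level 0.05, power 0.8, adherence 50/60/70%, ICC 0.1, 300 patients unclustered and about 500 clustered. From Population: 18 clusters initially. Equal cluster sizes are assumed throughout.

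**1. The plan's 300.** A two-group comparison of 50% with 70% (two-sided 0.05, power 0.8, continuity correction) needs 103 per arm, and 3 × 103 = 309, within 3% of 300. Without the correction it is 3 × 93 = 279. A three-group chi-square test needs 347, and has 73.6% power at 300. So 300 is reached only approximately, as a 50% v 70% comparison.

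**2. The plan's 500.** The implied design effect is 500/300 = 1.667. From DE = 1 + (m − 1) × ICC, with ICC 0.1:

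- m = 1 + 0.667/0.1 = 7.67 patients per cluster, or 500/7.67 ≈ 65 clusters.
- With 18 clusters, m = 500/18 = 27.8, DE = 1 + 26.8 × 0.1 = 3.68, and the effective sample size is 500/3.68 = 136.

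The 500-for-300 correction and the 18 clusters therefore do not fit together at ICC 0.1. With 18 clusters the effective sample size cannot exceed 18/0.1 = 180, however many patients are enrolled.

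**3. Type I error of the unadjusted test on patient counts.** With 2 degrees of freedom (df) the critical value is 5.991. Clustering inflates the statistic by DE, so the rejection rate under the null is P(χ²₂ > 5.991/DE) = exp(−2.996/DE).

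| 500 patients, ICC 0.1 | DE | Rejection of a true null |
|---|---|---|
| Plan's own correction (about 65 clusters) | 1.667 | 16.6% |
| 60 clusters | 1.733 | 17.8% |
| 45 clusters | 2.011 | 22.6% |
| 36 clusters | 2.289 | 27.0% |
| 24 clusters | 2.983 | 36.6% |
| 18 clusters | 3.678 | 44.3% |

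**4. Simulation check.** Beta-binomial data, ICC 0.1, 100,000 trials per setting, true adherence 50% or 60% in all arms:

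- 6 clusters of 28 per arm: the chi-square test rejects in 45.0% and 45.2% of trials; a cluster-level F test in 5.2% and 5.0%.
- 22 clusters of 8 per arm: the chi-square test rejects in 17.4% of trials at either rate; the cluster-level F test in 5.0% at either rate.

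**5. If the differences are changes from baseline.** The ICC of a change may be below 0.1. As an assumption, with 500 patients in 18 clusters: ICC 0.01 gives 9%, 0.02 gives 14% and 0.05 gives 28%.

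**6. Power of a valid test.** For 50/60/70% at ICC 0.1, the cluster-level F test has about 34% power with 18 clusters of 28, and about 74% with 66 clusters of 8.

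**The case against.** The strongest reply is that the protocol does state a cluster-level step, that the term chi-square could cover a cluster-adjusted or Wald version, and that a statistical analysis plan not shown here may say so. It is true that the link between the per-cluster differences and the test is undefined, so ignoring the clusters is the likely reading but not the only one. However, the protocol does not merely leave the method open. It names a test, and as worded that test is not suitable. If an adjusted version was meant, the sentence still has to change.

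The second reply concerns size, and it stands. A reader might infer that an error rate of 44% follows from the ICC alone, so that a false positive is close to a coin flip. The documents do not support that. The 44% also needs all 500 patients to come from 18 clusters, which the protocol calls only the initial set. The plan's own correction at the same ICC implies more and smaller clusters, and about 17%.

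Two further inferences go too far. Unequal cluster sizes would usually add to the inflation, but the protocol gives no size distribution from which to put a figure on it. And a rejection by the three-group test is not in itself a claim that decision support works, or that it changes anticoagulant prescribing. It could arise from a difference between the two intervention arms, and the outcome is guideline adherence, which also covers antiplatelet recommendations.

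**Conclusion.** The point holds. The protocol corrects its sample size for clustering and then names, as the sole test of the primary outcome, a chi-square test without cluster adjustment. On patient counts the nominal 5% test has a true error rate of about 17% at the plan's own design effect, more than three times the stated level. It reaches about 44% if the 500 patients all come from the 18 initial clusters, and lies between about 37% and 18% for 24 to 60 clusters.

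These figures assume ICC 0.1, equal cluster sizes and an analysis of endpoint proportions; any cluster count beyond 18 is an assumption. If changes from baseline are analysed and their ICC is lower, the inflation is smaller (about 9% to 28% for ICC 0.01 to 0.05 with 18 clusters), but the test is still anti-conservative. The defect is certain as a matter of wording; its exact size is conditional. Because it affects the only stated primary test, it should be corrected before the analysis.

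**What to change.** Replace the chi-square sentence with a primary test that respects the clusters. For example: calculate one adherence proportion per GP cluster and compare the arms by linear regression or analysis of variance with cluster-level df (18 − 3 = 15 if there are 18 clusters). A patient-level mixed model with a cluster random intercept and small-sample df would also serve. State whether the per-cluster differences are changes from baseline. Report risk differences between arms with 95% confidence intervals from the same model. State the expected number of clusters, so that it can be reconciled with the 500-for-300 correction.

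The change to the text is about one sentence plus these clarifications, with slightly more analysis work and no new data. The real price is visible uncertainty: intervals become wider, and with 18 clusters of 28 the power for 50/60/70% is about 34% rather than the planned 80%. Changing the test does not cause that shortfall. It comes from the small number of clusters at ICC 0.1, and the unadjusted test would hide it.

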**Outcomes**

The primary outcome is the difference in the proportion of patients with AF, treated in adherence to the guideline between groups 1, 2 and 3.
The secondary outcomes are the reasons GPs provide for deviating from the guideline and the manner in which they respond to required justification (intervention 2).

**Discussion**

This study will investigate the effectiveness of a decision support system in primary care by implementing a system that advises the general practitioner on antithrombotic treatment for stroke prevention in patients with atrial fibrillation. We will use a novel system that does not rely on pop-ups, but rather a sidebar that displays real-time messages concerning the actual patient, as studies have shown this to be the most effective timing for a CDSS ([10](#_ENREF_10)).

The success of the study depends on the ability of the system to attract the attention of the GP and on the quality of data stored in the EHR. One of our challenges was find­­ing the right mode of presentation, where messages are visible to the GP without interfering with their usual workspace. This meant we had to investigate computer use among GPs, especially which screen resolutions were used and how much space was available on their screen for our system. As it turned out, many GPs were working on older systems with low-resolution screens. We therefore had to adapt our system to actively show part of the message titles, the rest being entirely visible on demand. We hope this mode of presentation will not interfere significantly with the GP’s workspace, while remaining visible enough for the GP to notice.

**Guideline conversion**
We could not fully convert the complete guideline into our decision rule, as some elements were not available as structured data in the GP’s EHR. For instance, the finding “Fundus bleeds of the eye” has no code that can be used to identify it. Thus, we had to adapt our decision rule to work with the data that were available. Also, severe renal and liver failure were not defined with cut-off values, so we had to define these. These are important factors to consider during future guideline development, as decision support systems are expected to play an increasingly important role in healthcare. The recently introduced Logical Elements Rule Method (LERM) could play an important role in ensuring guideline-CDSS compatibility ([16](#_ENREF_16)).

**Reasons for deviation from the guideline**Based on findings in literature on this subject, we expect GPs will have a number of valid reasons to provide treatment different from the guideline ([8](#_ENREF_8), [17](#_ENREF_17)). These are expected to be in the following categories: patient preference, diagnostic uncertainty and contextual factors (e.g. medication prescribed by specialist). Almost all the other reasons we expect GPs to report will be related to incomplete registration. For instance, a contraindication for oral anticoagulation cannot be a reason to disregard the system's advice, because the system checks for contraindications. Thus, the GP needs to update EHR to reflect the latest clinical situation.

**Effect size and reasons for non-adherence**
We expect a 10% and 20% absolute effect size in intervention groups A and B, respectively. We hypothesize that the main reason for non-adherence is that there are too many parameters in this guideline to be evaluated effectively during a 10-minute visit. If a patient develops diabetes and reaches the age of 75, that has an impact on multiple guidelines. It is virtually impossible to know every guideline by heart, as there are currently one hundred Dutch GP guidelines, 10% of which are revised every year. Hence, the GP will often not be aware that the patient in fact needs to receive OAC instead of aspirin due to the fact that his or her CHADS2 score increased by two points.

**Conclusion**

This paper describes the protocol for a cluster randomized trial to study the effects of a clinical decision support system in patients with atrial fibrillation. The system is characterized by a non-interruptive presentation and real-time messages that are updated after each action the GP performs (if the action is part of the decision rule). We expect an absolute effect size of 10 to 20%, because current guideline adherence is low (around 50%) and the guideline might be missed or is difficult to evaluate during a patient visit in a busy practice.

**Trial Status:**

The CDSS plugin is currently being developed and tested. It is expected to be finished in March 2013, at which time a pilot period of one month will be started to identify any problems. After 1 month we will start collecting data.

**Competing interests**

The authors declare they have no competing interests.

**List of abbreviations**

AF – atrial fibrillation

CDSS – clinical decision support system

CRE – clinical rule engine

EHRS – electronic health records system

GP – general practitioner

ICPC – International Classification of Primary Care

OAC – oral anticoagulation

XML – Extensible Markup Language

**Acknowledgements**None

